### Study procedure and data collection

All healthy pregnant women receiving regular care at the obstetrical outpatient department of participating hospital will be counselled and asked at 12-28 weeks of gestation to participate in this study. General information will be collected and the anti-HPA antibody evaluation will be conducted after informed consent is received. The test of the antibody titre and antigen-specificity will be conducted at the production admission if the anti-HPA antibody test is positive. Genotyping of HPA will be further completed for anti-HPA antibody-positive mothers and their infants. Genotyping of HLA will be performed for mothers in both the exposure and non-exposure groups. Platelets of their newborns at day one of the birth will be counted, NAIT and ICH will be diagnosed.

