**Methods:**

A multicentre, prospective cohort study design will be used, and 55,497 pregnant women will be recruited for the first screening of the anti-HPA antibody at 12 to 28 weeks of gestational age. Subjects who are positive in the first screening for the anti-HPA antibody will be included in the exposure group. Re-tests of the antibody titre, antigen-specificity and genotyping of HPA and HLA will be conducted during admission. A ratio of 1:1 paired individuals with the same ethnicity and parity but testing negative for the anti-HPA antibody will be randomly selected to be included in the non-exposure group. NAIT will be diagnosed in the newborns on day one of the birth. The HPA of the neonates in the exposure group will also be genotyped by sequencing. Associations of maternal HLA with the occurrence of the anti-HPA antibody and correlation of the severity of NAIT with the titre of the anti-HPA antibody will be further analysed.

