### Recruitment and informed consent

The study is being conducted at 24 Grade-A Tertiary Hospitals in China. Subjects testing positive in the anti-HPA antibody test at 12-28 weeks of gestation will be included in the exposure group. A ratio of 1:1 paired individuals with the same ethnicity and parity but negative in the anti-HPA antibody test will be randomly selected to be included in the non-exposure group. The investigators will inform the participants about all aspects about the trial. The informed consent will include permission to collect blood samples from the mothers and their infants for antibody screening and genotyping of HPA and HLA, gathering data from their medical records and the storage of biological samples for a maximum of 10 years for additional analyses related to the current study. The participants will be informed that trial participation is voluntary and that they are free to withdraw at any time. All the investigators are aware of the guidelines for good clinical practice [8].

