### Anti-HPA antibody screening, identification and titration

The Monoclonal Antibody Solid Phase Platelet Antibody Test (MASPAT) Kit will be used in the screening of potential anti-HPA antibody-positive pregnant women [9]. The anti-HLA antibody and the anti-HPA antibody will be further distinguished by chloroquine-treated (i.e., HLA-depleted) platelets [4]. Two-fold serum dilutions in phosphate-buffered saline from undiluted to one in 1024 will be done to determine the titre of the anti-HPA antibody. Antigen specificity will be confirmed by LIFECODES Pak Lx (Immucor) [10].

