### Follow-up

There will be two follow-up visits after recruitment. One will be at the end of pregnancy before delivery, in which re-tests of the antibody titre, antigen-specificity and genotyping of HPA and HLA will be conducted in the mothers. The second follow-up will be after delivery, in which platelet counting and HPA genotyping of the newborns will be performed and NAIT will be diagnosed and graded.

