Although HLA-DRB3*01:01 is highly associated with the incidence of HPA-1a alloimmunization, it cannot be used to differentiate high- and low-risk pregnancies or to guide antenatal treatment in affected families [18]. Instead, the titre of the anti-HPA antibody has been reported to be a much better indicator of the severity of NAIT. The levels of the anti-HPA antibody have significant correlations with the risk [19] and the severity of neonatal thrombocytopenia [20]. When the antibody titre is ≥1:64 for HPA-5b in Japanese [19] and ≥1:32 [20] for HPA-1a in Caucasians, NAIT is significantly more severe. In this study, we also hope to find a Chinese-specific cut-off antibody titre for the prediction of the severity of NAIT and to provide a means to evaluate the necessity of antenatal treatment.

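### The only dated antibody titre is at the end of pregnancy or delivery admission, which cannot by itself support a cut-off for judging antenatal treatment in the same pregnancy

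*Protocol article*

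**What the plan says.** Exposure is set by the screening test: "Subjects testing positive in the anti-HPA antibody test at 12-28 weeks of gestation will be included in the exposure group" (Recruitment and informed consent).

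The titre is placed later, in three sections:
- Study procedure and data collection: "The test of the antibody titre and antigen-specificity will be conducted at the production admission if the anti-HPA antibody test is positive".
- Abstract, Methods: "Re-tests of the antibody titre, antigen-specificity and genotyping of HPA and HLA will be conducted during admission".
- Follow-up, first visit: "One will be at the end of pregnancy before delivery, in which re-tests of the antibody titre, antigen-specificity and genotyping of HPA and HLA".

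The laboratory section gives the dilution series but no sampling time: "Two-fold serum dilutions in phosphate-buffered saline from undiluted to one in 1024 will be done to determine the titre of the anti-HPA antibody".

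The titre has two uses. Table 1 lists, as a secondary objective, its relationship with the severity of NAIT and names no time point. The abstract and the Discussion add the hope of a Chinese-specific cut-off that would predict severity and also serve "to provide a means to evaluate the necessity of antenatal treatment".

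Antenatal treatment is left to current practice (Methods/design). Consent covers "the storage of biological samples for a maximum of 10 years for additional analyses related to the current study".

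**The concern.** A cut-off meant to inform a treatment decision has to be estimated from a measurement that exists when the decision is taken. Antenatal treatment is decided before birth. The titre that the article dates is taken when the woman is admitted to deliver, or shortly before.

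Two things follow if the schedule is applied as written. First, the threshold would be estimated at one stage of pregnancy and applied at another, and nothing in the article shows that titre is stable between them. Second, because treatment under current practice is allowed during the study, the delivery titre of any treated woman is a post-treatment value.

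What is at stake is the reach of the conclusion. The study could report that delivery titre goes with severity, but could not say from that result alone which titre earlier in pregnancy should prompt consideration of treatment. The titre is also named among the primary outcome variables, so its sampling time ought to be unambiguous.

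**Working it through.** The timing point is a comparison of sections. Arithmetic is needed only for the number of women concerned.

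**1. Sampling times side by side**

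| Section | Measurement | Time |
|---|---|---|
| Recruitment; Study procedure | antibody screening | 12-28 weeks |
| Study procedure | titre and specificity, called a test | delivery admission |
| Abstract, Methods | titre and specificity, called re-tests | during admission |
| Follow-up, first visit | titre and specificity, called re-tests | end of pregnancy, before delivery |
| Screening, identification and titration | dilution method | none given |

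All three dated titrations are late, and none is tied to the 12-28-week sample.

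**2. Does 're-tests' establish an earlier titre?** It hints at one. But the procedure section puts the test itself at admission. The phrase in the abstract and Follow-up can also be read to cover HPA and HLA genotyping, for which no earlier test is described either. The wording leaves an early titre possible but does not schedule it.

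**3. Gap between screening and the dated titre.** Assuming delivery at 38 to 40 weeks (the article gives no figure), the gap runs from 38 − 28 = 10 weeks to 40 − 12 = 28 weeks.

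**4. Which use survives?**
- Titre against severity (Table 1): no time point is named, so a delivery titre serves.
- Cut-off for antenatal treatment in the same pregnancy (abstract and Discussion): the dated titre comes too late to be the predictor.

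**5. Number of women**
- The plan's own figure first. With NAIT in 16.7% against 2.5%, two-sided α 0.05 and β 0.1, the cohort formula gives 89 per group. Then 89 × 1.1 = 97.9, which rounds to the stated 98. And 98 / 0.0019 = 51,579, against the stated 51,578.
- Antibody-positive women expected in the full cohort: 55,497 × 0.0019 = 105.4, about 105.
- After the plan's 10% dropout: 105.4 × 0.9 = 94.9, about 95.
- NAIT cases at 16.7%: 105.4 × 0.167 = 17.6 before dropout and 94.9 × 0.167 = 15.8 after it.

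These counts show the size of the group. The timing argument does not depend on them.

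**The case against.** **An earlier titre may exist.** The article condenses a fuller protocol, two sections say 're-tests', and an antibody evaluation follows consent at 12-28 weeks. This stands in part. A reader might infer that no early titration is done at all, but the article does not establish that. It establishes conflicting wording and the absence of any dated early titre.

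**The listed objective is met.** This stands. A reader might infer that the titre objective fails, but Table 1 asks only for a relationship with severity, and the planned regression of severity on titre can use a delivery value. The antenatal aim is outside Table 1 and is worded as a hope. It still appears in both the abstract and the Discussion, so readers will expect the study to address it.

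**A delivery titre could inform the next pregnancy.** The Discussion says that antenatal treatment can at present be offered only in later pregnancies, after an affected child. That is a fair limit on the point, which is why it is confined to decisions in the same pregnancy. The study's stated interest in whether pregnant women should be screened makes the same-pregnancy use relevant.

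**Few women may be treated.** This also stands. A reader might infer that treatment has altered the delivery titre of the whole exposed group. The article does not say how many women are treated, and it plans to analyse women with previous or familial NAIT hierarchically. The treatment argument applies only to those actually treated.

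**Women lost before admission.** They would have no dated titre, but most would also lack the newborn platelet count. They could not enter the severity analysis either way, so this adds little.

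**Conclusion.** The point holds in a limited form. As written, the only dated titre and specificity measurement falls at the end of pregnancy or at delivery admission. It is adequate for the listed association with severity. It is not adequate, by itself, for a cut-off to evaluate antenatal treatment in the same pregnancy.

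The analysis rests on about 105 antibody-positive women at the planning rate of 0.19%. The article gives no data on how titre changes between screening and delivery, so the size of any error in carrying a delivery cut-off back to the screening window cannot be stated. The conclusion does not need such a figure, because it follows from the order of events.

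It assumes that the schedule in the article is the one followed. If the full protocol already titrates the 12-28-week sample, what remains is a wording conflict. This is a worthwhile, low-cost improvement and not a flaw in the study's listed objectives.

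**What to change.** 1. Reconcile 'test' in Study procedure and data collection with 're-tests' in the abstract and Follow-up, and state when titre and specificity are first measured.
2. Titrate the 12-28-week screening sample of each screen-positive woman where enough serum is retained, and record gestational age at sampling.
3. Use that early titre for the antenatal cut-off analysis. Keep the delivery titre for the association with severity.
4. If early titration is not done, limit the conclusion to an association at delivery and drop the antenatal-treatment claim from the abstract and the Discussion.

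The cost is about 105 extra titrations at 0.19%, plus wording. The number rises if the antibody rate is higher. It also depends on screening serum being kept: the consent covers storage of biological samples for related analyses, but the article does not say which samples or what volume. The change alters no treatment rule.

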### General information

General data, maternal health history and delivery records will be obtained from the medical records. Confounding factors affecting the platelets of the newborns will be collected by telephone interview. All of the information will be recorded in the Case Report Form (CRF).

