## Methods/design

This study is a nationwide, prospective, non-interventional, multicentre cohort study. The objectives are listed in Table 1. The survey and data collection will provide baseline data on NAIT in China and help form an appropriate clinical screening procedure.

**Table 1 Tab1:** Study objectives

Primary objectives	
• The positive incidence of the anti-HPA antibody in pregnant Chinese women.	
• The morbidity of NAIT in anti-HPA antibody-positive pregnant women in China.	
Secondary objectives	
• Antigenic specificity of anti-HPA antibodies.	
• Association of the anti-HPA antibody with HLA genotype.	
• The relationship between the titre of the anti-HPA antibody and the clinical symptom severity of NAIT.	

This study is non-interventional. The assignment of subjects to antenatal treatments (such as intravenous immunoglobulin and intrauterine fetal platelet transfusion) or a particular delivery planning is not decided in advance but instead falls within current practice.

Study recruitment started primarily at the sponsor centre at The Second Affiliated Hospital of The Third Military Medical University on 1 November 2016. All other centres initiated consecutive recruitment before the end of January 2017. Recruitment is expected to be completed before December 2018.The goal is to enrol 55,497 women at 12-28 weeks of gestation.

The study subjects will be pregnant Chinese women and their newborns. Inclusion and exclusion criteria are listed in Table 2. Subjects with NAIT in a previous pregnancy or a positive family history of first degree relatives will not be excluded but will be analyzed hierarchically.

**Table 2 Tab2:** Inclusion and exclusion criteria

Inclusion criteria
• Pregnant women 18–50 years of age
• Pregnant women at 12-28 weeks of gestation between 1 January 2017 and 31 December 2018.
• Willingness of the mother to give birth in a participating hospital
• Willingness to participate in the study
Exclusion criteria
• Pregnant women unwilling to participate in the study
• Pregnant women planning to prematurely terminate the pregnancy

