### Diagnosis and grading of NAIT

NAIT is defined as a platelet count in the neonates of less than 150 × 10^9^/L and the HPA is incompatible with the mother. When the platelet count is less than 50 × 10^9^/L, we will grade the NAIT as severe. These cases are distinguished from cases of moderate (platelet count 50 × 10^9^ - 100 × 10^9^/L) or mild NAIT (platelet count 100 × 10^9^-150 × 10^9^/L) [5].

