### Variable and potential confounders

The primary outcome variables will be the titre of the anti-HPA antibody of the mothers and the platelet count of the newborns. The secondary outcome variables will include the pregnancy number. The potential confounding variables that will be measured will include nationality, maternal history (e.g., parity, still birth and abortion), allogenic platelet transfusion history and diseases leading to a decreased platelet count in the mother (e.g., idiopathic thrombocytopenic purpura, eclampsia and gestational diabetes mellitus) and in the newborns (e.g., intrauterine growth retardation, intrauterine infection and neonatal asphyxia).

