### Statistical analysis

The data will be analysed using SPSS V18 (SPSS, Chicago, Illinois, USA). 95% confidence levels will be set to test for significance. Descriptive statistics will be used to analyse the general data, the positive incidence of the anti-HPA antibody and the morbidity of NAIT. The frequency of thrombocytopenia between groups will be compared by using the χ^2^ test. The χ^2^ test will also be used in the analysis of the associations between the pregnancy number (or mother HLA genotype) and the incidence of the anti-HPA antibody. The correlations between the titre of the anti-HPA antibody and the severity of NAIT will be analysed by using the multiple regression analysis.

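### Newborn conditions that can lower the platelet count are taken from a telephone interview although the hospital record is available; chart abstraction would protect the adjusted analyses.

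*Protocol article*

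**What the plan says.** The General information section of the protocol article names two data sources. For most items: "General data, maternal health history and delivery records will be obtained from the medical records". For the factors at issue: "Confounding factors affecting the platelets of the newborns will be collected by telephone interview".

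The section on variables and potential confounders lists diseases that reduce the platelet count, with these examples for the newborn: "intrauterine growth retardation, intrauterine infection and neonatal asphyxia".

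Three other places bear on the choice of source and on its use:

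- Consent (Recruitment and informed consent) includes "gathering data from their medical records".
- The inclusion criteria (Table 2) require "Willingness of the mother to give birth in a participating hospital".
- The Statistical analysis section says: "The frequency of thrombocytopenia between groups will be compared by using the χ^2^ test". It analyses titre against NAIT severity by multiple regression and names no covariates for either analysis.

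The article does not say when the interview takes place, what the mother knows by then about her antibody result or her infant's count, or whether her answers are checked against the chart.

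**The concern.** Growth retardation, intrauterine infection and asphyxia are diagnoses that clinicians make and document. The plan assigns newborn confounders of this kind to parental report, while it takes delivery data and maternal history from the record. Misclassification has two routes to harm:

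- **Equal misreporting.** If the condition is unevenly spread across the groups or titre levels compared, adjusting for a poorly measured version leaves part of the confounding in place.
- **Unequal misreporting.** A mother whose infant had a low count may have had more explanation and more reason to look for causes. All newborns with thrombocytopenia also have an ultrasound examination for intracranial haemorrhage. Adjusting for a variable recorded in this way can create bias where none existed.

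At stake is the titre-severity analysis, on which the hoped-for cut-off titre depends, and any group comparison that adjusts for these conditions.

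**Working it through.** **No planned figure to reproduce.** The article quantifies neither recall nor the frequency of these conditions, and no sample-size input depends on the data source. For context, the cohort formula at 16.7% versus 2.5%, two-sided alpha 0.05 and 90% power gives

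(1.96·√(2·0.096·0.904) + 1.2816·√(0.167·0.833 + 0.025·0.975))² / 0.142² = 88.4, so 89 per group.

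89 × 1.1 = 98, the stated number of antibody-positive women. About 89 × 0.167 = 15 affected infants are then expected in that group, so the severity analysis rests on few events.

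**Where the confounders can enter**

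| Element of the plan | Uses newborn confounders? |
|---|---|
| NAIT definition: platelet count below 150 × 10^9/L "and the HPA is incompatible with the mother" | No |
| Chi-squared comparison of thrombocytopenia | No covariates named |
| Multiple regression of severity on titre | Possible; covariates not named |
| Any adjusted group comparison | Yes, if done |

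**Illustration. Every input is assumed.** Baseline risk b = 0.02; the condition multiplies risk by r = 5; the true ratio between the groups is R = 4 (R = 1 in the reference group); specificity of the report t = 0.99. The condition's prevalence q and the sensitivity s of the report vary. The two groups may be read as antibody-positive and antibody-negative or, as a two-level simplification, as higher and lower titre.

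In each group:

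- share reported with the condition = q·s + (1−q)(1−t)
- risk in that stratum = [q·s·b·r·R + (1−q)(1−t)·b·R] / share
- the stratum reported without it uses (1−s) and t in place of s and (1−t)

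The adjusted ratio standardises both groups to the average of their two reported distributions. Where recall depends on the infant's count, s is applied separately to infants with low and normal counts.

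*Worked case 1: q = 10% in both groups, s = 0.9 versus 0.6.* Reported shares are 0.099 and 0.069, giving weights 0.084 and 0.916. Stratum risks are 0.3709 and 0.08355 in the first group, and 0.08957 and 0.02344 in the second.

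(0.084·0.3709 + 0.916·0.08355) / (0.084·0.08957 + 0.916·0.02344) = 0.1077 / 0.02899 = 3.71

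*Worked case 2: q = 10% in both groups, s = 0.9 if the count is low and 0.6 if normal.* Reported shares are 0.081 and 0.072, giving weights 0.0765 and 0.9235. Stratum risks are 0.4533 and 0.08192, and 0.1275 and 0.02028.

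(0.0765·0.4533 + 0.9235·0.08192) / (0.0765·0.1275 + 0.9235·0.02028) = 0.1103 / 0.02848 = 3.87

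**Results (true ratio 4.00)**

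| Prevalence | Crude | s = 0.9 | s = 0.7 | s = 0.5 | 0.9 vs 0.6 by group | 0.6 vs 0.9 by group | 0.9 low count, 0.6 normal |
|---|---|---|---|---|---|---|---|
| 10% vs 10% | 4.00 | 4.00 | 4.00 | 4.00 | 3.71 | 4.31 | 3.87 |
| 15% vs 10% | 4.57 | 4.10 | 4.22 | 4.34 | 3.84 | 4.58 | 3.93 |
| 20% vs 10% | 5.14 | 4.19 | 4.43 | 4.66 | 3.95 | 4.82 | 3.97 |

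- The crude ratio does not depend on recall in any row.
- Equal prevalence with equal recall gives no bias.
- Equal prevalence with unequal recall biases the adjusted result although the crude one is right.
- Unequal prevalence with imperfect equal recall leaves residual confounding.

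**The case against.** The strongest reply is that the two main NAIT results cannot be touched. The diagnosis rests on a platelet count and HPA incompatibility, and the group comparison is a chi-squared test with no covariates. That is correct. A reader might infer that recall error biases the NAIT comparison, or that an unreported cause inflates the NAIT count. The document supports neither: the definition excludes no other cause, so an infant with perfectly documented asphyxia would still be counted.

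Second, titre is measured only in antibody-positive women, so the titre regression contains no control mothers. Recall that differs between antibody-positive and antibody-negative women therefore cannot act there. This also stands. Only recall that differs by the infant's count, or plain misclassification, remains relevant, and only if these conditions are covariates.

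Third, the article does not list the interview items one by one, does not say that the record holds these diagnoses, and does not rule out a chart check. It is also a condensed text, and the case report form is not shown. These points limit certainty. Even so, the article positively assigns a source to newborn confounders, so this is a stated choice and not an omitted detail. That the record holds the diagnoses is an inference, though a sound one, from delivery in participating tertiary hospitals and the use of delivery records for other items.

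**Conclusion.** The point holds as a cheap improvement. The stated source for newborn confounders is weaker than one the study already has permission to use. Misreporting can leave residual confounding or add bias in the titre-severity regression and in any adjusted group comparison. It does not alter the NAIT definition or the crude comparison.

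The size is unknown. In the illustration, imperfect recall gives adjusted ratios from 3.71 to 4.82 against a true 4.00, with no bias when prevalence and recall are both equal. That range depends wholly on the assumed prevalences, risks and recall, and bias in either direction is possible. The conclusion also assumes that variables collected as confounders are meant to be used as such.

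**What to change.** Change the sentence under General information so that the newborn conditions listed under variables and potential confounders are abstracted from the obstetric and neonatal records, on the same form in the exposure and non-exposure groups. Keep the telephone interview only as a supplement, for items that the record does not hold or for births elsewhere. If charts are already used in practice, correcting the text is enough.

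The cost is a small amount of extra chart abstraction. Consent already covers the records, and neither the sample size nor patient care changes.
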